### **Main treatment options for visceral leishmaniasis.**

Treatment of VL cases in Eastern Africa always presents with challenges such as patients coming late when they are extremely ill and may die during treatment due to the illness as well as toxicity of the drugs used. The other challenges include availability of drugs, drug resistance, and cost of treatment (drugs and hospitalization). In VL endemic areas, facilities may not be available for accurate diagnosis and follow up, and the increasing prevalence of HIV co-infection is an additional challenge, particularly in Ethiopia.

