### **EFFICACY ASSESSMENT**

Efficacy will be assessed using clinical, haematological, biochemical and parasitological responses.

- **Clinical Assessment**

The clinical evaluation will involve measuring the spleen size by palpation below the left coastal margin, temperature, blood pressure, body weight on days 0, 7, 14, 21 and end of treatment (18, 22, 31), 3 months and 6 months post treatment.

ECG and audiometry will be done at baseline, day 14, end of treatment and 6 months follow-up, in selected sites.

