## **FINAL VERSION LEAP 0104 31 JULY 2004 CONFIDENTIAL**

- Haematological and biochemical assessment

Blood will be analyzed for haemoglobin, WBC, platelets, urea, creatinine, and liver function tests on days 0, 7, 14, 21 and end of treatment (18, 22, 31), 3 months 6 months post-treatment.

- Unanalysis

Urinalysis will be performed on days 0, 7, 14, 21 and end of treatment (18,22,31) 3 months and 6 months post-treatment.

- Parasitological assessment

Parasitological assessment involves aspirating the spleen, lymph node or bone marrow at baseline, end of treatment (18, 22, 31 days depending on treatment arm) on, and at 3 months and 6 months follow up visits for all study patients. In addition, at selected sites aspirates will be cultured. Each patient will have a maximum of four aspirates. Patients who are clinically well with no signs or symptoms of VL and no palpable lymph nodes / spleen at the three months visit do not to have any aspirate at this visit. All patients will have an aspirate at 6 months post treatment.

The source of parasitological specimens should remain unchanged throughout the treatment and follow up periods, unless the spleen / lymph node initially chosen as the source of parasitological specimens becomes unpalpable, in which bone marrow aspirate should be performed.

Since bone marrow, lymph node and splenic aspirates are invasive procedures, these should only be performed at other times if clinically indicated.

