#### **Analysis**

In the analytical approach intention to treat will be used. The aim is to estimate the difference in treatment outcomes for the three arms. The intention to treat analytical method will take care of events such as patient withdrawal from the trial, failure to comply with treatment, change in treatment and lost to follow-up.

There are two basic options:

Analyse final outcome only for those who complied perfectly with each treatment

Analyse data for all subjects in the groups to which they were randomized. This is referred to as 'Intention to treat' analysis or the 'pragmatic approach'.

The second option will be adopted, analysis will be carried out according to the original treatment assignment regardless of adherence to treatment or protocol.

There will be no exclusion of patients or events. Drop-outs will be checked to establish whether they were systematic or non-random. The analysis will, as much as possible stick to the protocol to avoid data dredging as part of post ad hoc analysis.

Note: Specific country analysis will be of little value because it lacks power. The data will have to be pooled for it to achieve the necessary power in the efficacy analysis.

Summary statistical measures to be computed

The summary statistics will include the  $\chi^2$  and risk ratios per arm for the overall efficacy comparison. The analysis and interpretation will heavily rely on confidence intervals of the cure rates among the three arms of the RCT. Other estimations to be made will be the calculation of the power finally achieved by the trial. This will be followed by the presentation of the results in terms of basic descriptive statistics and statistical diagrams. Finally multivariate analysis will be carried out to establish the socio-demographic factors associated with the main parameters.

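### Day-0 severity values measured in every patient have no role in the comparison of arms; a pre-specified adjusted estimate would add a little precision at almost no cost

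*Protocol*

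**What the plan says.** Under Data Collection, Storage and Analysis (Analysis), the protocol adopts intention to treat and sets the efficacy comparison as chi-square and "risk ratios per arm for the overall efficacy comparison". It adds: "The analysis and interpretation will heavily rely on confidence intervals of the cure rates among the three arms of the RCT". No covariate is attached to any of these. The section ends with the only multivariable analysis it names: "Finally multivariate analysis will be carried out to establish the socio-demographic factors associated with the main parameters". Treatment arm is not mentioned as a term in that model.

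The Efficacy Assessment section schedules baseline measurements for all patients. On the clinical side: "The clinical evaluation will involve measuring the spleen size by palpation below the left coastal margin, temperature, blood pressure, body weight on days 0", and then weekly. On the laboratory side: "Blood will be analyzed for haemoglobin, WBC, platelets, urea, creatinine, and liver function tests on days 0", and then weekly. ECG, audiometry and culture are restricted to selected sites; these measurements are not. No section gives their day-0 values a role in comparing the arms.

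**The concern.** The protocol itself expects patients to differ in how ill they are. Among the challenges of treatment in the region it lists "patients coming late when they are extremely ill and may die during treatment". Randomisation is restricted within country, so disease severity is balanced between arms only on average. If severity predicts cure at 6 months, an adjusted estimate would be somewhat more precise than the planned one and would correct for chance imbalance on the covariates used.

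The data for this are already collected. The Analysis section is also not silent on modelling: it chooses one class of factors, and that class leaves out the clinical severity measures. Because the same section says the analysis should keep to the protocol to avoid data dredging, a severity-adjusted estimate added later would look post hoc. What is at stake is some precision and robustness. The validity of the trial is not in question.

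**Working it through.** **1. The plan's own figures (Sample size Determination).** Inputs: cure 95% v 85%, two-sided 5%, power 90%, k = 10.5, 15% attrition, 20% extra for Ethiopia.
- Per arm: 10.5 × (0.85×0.15 + 0.95×0.05) / 0.10² = 10.5 × 0.175 / 0.01 = 183.75, so 184. This agrees with the protocol.
- After attrition: 184 / 0.85 = 216.5, so 217. This agrees.
- Total: 3 × 217 + 0.20 × 217 = 694.4, so 695. This agrees. Rounding to blocks gives 705, or 235 per arm.
- Evaluable after 15% loss: 235 × 0.85 ≈ 200 per arm.

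None of these figures uses a covariate.

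**2. Is the unadjusted comparison valid?** Trials were simulated with no true difference (85% v 85%), 200 per arm and a severity score with a log-odds of 0.5 to 1.0 per SD (1,500 runs per setting). The unadjusted test rejected in 5.0-5.6% of runs, which is nominal within simulation error.

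**3. How much would adjustment gain?** The protocol gives no prognostic strength for any day-0 value, so a range is assumed: one severity score with a log-odds of about 0.5 to 1.1 per SD. The estimator is a logistic model with arm and score, standardised to a risk difference, compared with the unadjusted difference.

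| Analysis set | Cut in variance of the risk difference |
|---|---|
| 200 evaluable per arm, no loss | about 2-11% |
| 235 per arm, 15% loss counted as failure, loss unrelated to severity | about 1-3% |

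The second row follows the protocol's own rule. Its Analysis section excludes no patient, and Criteria for Patient Withdrawal analyses withdrawn patients, including those lost to follow-up, as failures. Loss unrelated to severity adds failures that severity cannot predict, so the gain shrinks.

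**4. The same gain as interval width (95% half-width for one pair of arms).**
- 200 evaluable: 1.96 × √(0.175/200) = 5.8 points. Multiplying by √0.98 to √0.89 gives 5.7 to 5.5 points.
- 235 with loss as failure: the cure rates become 0.85×0.95 = 0.8075 and 0.85×0.85 = 0.7225. The half-width is 1.96 × √((0.8075×0.1925 + 0.7225×0.2775)/235) = 7.63 points. Multiplying by √0.99 to √0.97 gives 7.59 to 7.51 points.

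**5. Power for a 10-point difference at 200 evaluable per arm.** In simulation (log-odds 0.5 to 1.0 per SD), power was about 92% unadjusted and 93-94% adjusted.

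**6. Chance imbalance.** Assume a severity factor present in 30% of patients that lowers cure by 10-20 points. Two arms of 200 differ in its prevalence by more than 1.96 × √(2×0.3×0.7/200) = 9.0 points in 1 trial in 20. That shifts the observed difference by 0.09 × 10 to 0.09 × 20, or 0.9 to 1.8 points, against a half-width of 5.8 points.

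**The case against.** The strongest reply is that an unadjusted comparison of randomised arms is a legitimate primary analysis, and that the choice of covariates is commonly left to a statistical analysis plan, which is not at hand. The first part stands in full. The second stands in part: the Analysis section does not forbid adjustment, but it does state which factors will be modelled, so the choice is made rather than deferred.

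Other parts of the reply also stand:
- The evidence for prognostic strength is thin. The passage on malnutrition and anaemia under Clinical Aspects concerns progression from infection to disease, not cure under treatment. The passage on very ill patients describes VL patients in general and attributes deaths to drug toxicity as well as to illness.
- The Exclusion Criteria remove severe malnutrition, haemoglobin below 5 g/dl, low white cells and platelets, and serious concomitant disease. This narrows the range of severity, so the upper end of the assumed strengths is optimistic.
- A 9-point imbalance is a 1-in-20 event by construction, and the unadjusted confidence interval already allows for such variation. It is not an additional bias.
- Previous VL treatment is not a usable covariate. The exclusion covers only the last 6 months, and nothing shows that lifetime history is recorded.

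A reader might infer that the socio-demographic sentence is what keeps severity out of the comparison. It is not: that sentence describes a search for predictors, while the comparison is unadjusted for every covariate and would stay so if severity were added to that search. Nor is the protocol's thinking purely socio-demographic. Sample size Determination speaks of controlling for HIV/AIDS, and a subset analysis by HIV status is planned. Those are separate matters from day-0 severity.

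**Conclusion.** The point holds as a low-cost improvement. The protocol plans an unadjusted comparison and one model that estimates no treatment effect, while day-0 spleen size, body weight and haemoglobin go unused in comparing the arms. A reader might go further and call the planned comparison biased or its error rate inflated. The documents do not support that, since randomisation protects it and the simulated type I error is about 5%.

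The size is a variance reduction of about 2-11% at 200 evaluable per arm, and about 1-3% under the protocol's rule of analysing everyone with loss as failure. There is also modest protection against chance imbalance. These figures rest on assumed prognostic strengths, on 95% v 85% cure and, for the smaller range, on loss unrelated to severity. The smaller range is the one to expect if the plan is followed as written.

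**What to change.** In the Analysis section, keep the unadjusted comparison and add a pre-specified adjusted one:
- Name age, spleen size and haemoglobin, as recorded at baseline, as the covariates.
- Fit one logistic model for 6-month cure with treatment arm and these covariates in all randomised patients.
- Report each between-arm risk difference by standardisation, with its 95% CI, beside the unadjusted result.
- Label the socio-demographic model exploratory, and do not use previous VL treatment as a covariate.

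The cost is a few lines of text and one extra model. Spleen size and haemoglobin are already scheduled on day 0, and age is needed for eligibility, so no patient or procedure is added. The list must stay short because failures are limited. At the planning rates there are roughly 10-30 per arm among 200 evaluable. If the 15% lost (about 35 of 235) count as failures, there are roughly 45-65.

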## **QUALITY CONTROL AND QUALITY ASSURANCE**

All study sites and data generated during the study will be regularly monitored by GCP trained clinical monitors. Wherever possible, CRF data will be verified against hospital source data, for example patient notes or laboratory reports, etc.

## **ETHICAL CONSIDERATIONS**

The study protocol together with patient information and consent forms will be submitted to the local scientific and ethics committee and any other regional or national regulatory authorities as required in the three countries, Kenya, Sudan and Ethiopia, before the study starts and any patient receives study medication.

The patients who participate in this study will be hospitalized and under close monitoring. The invasive diagnostic methods used in the study are those used in

## **FINAL VERSION LEAP 0104 31 JULY 2004 CONFIDENTIAL**

normal clinical practice when treating patients with VL. However, the frequency of testing might be increased depending on the patient's response to treatment.

Children will be included in this study because they represent more than 50% of VL cases in this region.

The effective treatment of VL benefits not only the individual patient but also the community by reducing the reservoir of infection for onward transmission by the sandfly vector. The evaluation of new and better treatments for VL, including shorter courses and combinations is anticipated to have a positive effect on development of parasite resistance and will reduce hospitalisation costs. If paromomycin is found to be efficacious and safe, it will be registered for the treatment of VL, providing a new alternative to treatments already available.

Patients will experience some pain while blood is drawn during venepuncture. The amount of blood to be drawn will be 10 mls before treatment and 7 mls at each subsequent visit, with a total of 42 mls (PM alone and a combination of PM and SSG), 49 mls (SSG alone) over the 6 months study period.

SSG has been extensively used in Sudan, Ethiopia and Kenya. Known adverse events include cardiac, muscle, joint and renal toxicity. PM has been used in clinical trials in Sudan and Kenya during the 1990's, and more recently in humanitarian emergency setting in Sudan. Known adverse events of the aminoglycosides include ototoxicity and renal toxicity.

Patients who are found to be HIV positive will be offered anti retroviral treatment at no cost in accordance with national guidelines for treatment.

A Data Safety and Monitoring Board (DSMB) will be set up to regularly review safety data.

Patients will be reimbursed for travel to and from the study site and will not receive any payment for trial participation. Any medication that is required during the trial period will be provided free of charge to the patient.

### **INSURANCE AND LIABILITY**

DNDi is insured to indemnify the collaborating investigator for any injury or harm which occurs during the performance of the trial according to the protocol signed

by the investigator. Furthermore, DNDi will in accordance with the declaration of Helsinki on Ethical principles for medical research involving human subjects, make all reasonable efforts to protect patients from any harm which may occur during the trial, and will wherever possible ensure that any patient that does suffer harm will receive the best possible treatment available in that country to alleviate their suffering.

## **TIME FRAME**

The study is expected to start in October 2004 and will last 12 to 18 months (6-12 months recruitment period plus 6 months follow up)

